**Secondary outcomes**		
Percentage days of heavy drinking	TLFB	X
Alcohol Misuse	• Alcohol Use Disorders Identification Test (AUDIT) [26] • Alcohol, Smoking and Substance Involvement Screening Test (ASSIST) [32]	X
Psychological distress	Kessler-10 (K10) [27]	X
Depression	Mental Health Assessment Inventory (MHAI), depression sub-scale [33]	X
Anxiety	Mental Health Assessment Inventory (MHAI), anxiety sub-scale [33]	X
PTSD	Mental Health Assessment Inventory (MHAI), PTSD sub-scale [33]	X
Functional disability	Mental Health Assessment Inventory (MHAI) [33]	X
Perpetration of intimate partner violence	United Nations Multi-Country Study on Men and Violence [34]	X
Health economics indicators	• EuroQol 5 dimensions 5 Levels (EQ-5D-5L) [42] • Subjective wellbeing [35] • Oxford Capabilities Mental Health questionnaire (OxCAP-MH) [36] • User cost questionnaire	X

**Table 3 Tab3:** Details on CHANGE Intervention Trial Outcome Measures (table adapted from Van Der Boor et al., 2024 [23])

Instrument	Description	Outcome	Contextual validity
Timeline Followback	Diary method to retrospectively assess daily estimates of drinking	Percentage days abstinent (PDA): Proportion of past 14 days on which participant was abstinent; analysis based on distribution. It also allows measurement of percentage of days of heavy drinking	Validated for alcohol use assessment including in Ukraine [43]
AUDIT	Ten-item questionnaire to measure alcohol intake, identify potential dependence on alcohol; and experiences of alcohol-related harm. Each item assessed on a scale of 0 to 4	Mean score, and dichotomous (medium vs. high risk) as secondary outcome	Validated for the current project with Ukrainian and Russian speaking men living in Ukraine, paper forthcoming
ASSIST	Eight-item screening questionnaire on estimates of alcohol use, tobacco products, and other drugs across the lifetime and in the past three months. Measured on a scale of 0 to 7	Mean score	Validated in a multisite international study covering Australia, Brazil, India, Thailand, United Kingdom, USA, and Zimbabwe [44]
K10	Ten-item scale on non-specific psychological distress, scored on a scale of 1 to 5	Mean score	Validated in Ukraine including amongst war-affected Ukrainians [45, 46]
MHAI	Thirty-two item scale on depression, post-traumatic stress, anxiety, functioning and alcohol use	Mean score	Locally validated measure with good psychometric properties [33]

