### Sample size {14}

A sample size of 500 enrolled participants (250 in each arm with 1:1 allocation) will provide 90% power (alpha = 0.05) to detect a difference in participants’ PDA from alcohol at follow-up of 55% in the EUC arm vs 68% in the CHANGE arm. This assumes participants’ PDA from alcohol is distributed with a standard deviation of 37% in both arms [37]. Both the effect size and the standard deviation are based on the Counselling for Alcohol Problems (CAP) trial (54% vs. 69%). The sample size calculation accounts for 20% loss to follow-up at 3 months and is based on Nadkarni et al. 2017 [37].

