## Statistical methods

### Statistical methods for primary and secondary outcomes {20a}

In line with the protocol published by van der Boor et al. [23], a statistical analysis plan will be written by the statistician based at the London School of Hygiene and Tropical Medicine and approved by the Data Safety and Management Board (DSMB) prior to unmasking of the data and analysis. The quantitative data will be analysed using Stata 17.0. An initial analysis will be conducted to compare participants who did and did not provide consent for participation following initial screening. Further descriptive analysis will then be carried out to compare the baseline characteristics of the participants. If substantial baseline imbalances exist in characteristics that are likely to affect outcomes, these will be adjusted a priori to the outcome analyses.

Binary outcomes will be analysed using logistic regression or negative binomial regression, depending on the distribution. Marginal standardization and delta methods [38] will be used to calculate adjusted risk ratios if logistic regression is used. Continuous outcomes will be analysed using linear regression, and adjusted mean differences reported. Before analysis, distributions of all outcome variables will be inspected, and if necessary, transformations or other modelling options will be considered.

All models will be adjusted for baseline characteristics that differ between the arms as determined by the descriptive analysis and the baseline measures. *P* values will not be used to identify differences between arms at baseline, as these are assumed to be at random. Fully adjusted (if appropriate) model results will be presented and reported using CONSORT guidelines [39]. Intention to treat principles will be used for the primary analysis.

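### Beyond baseline PDA, covariates enter the models according to observed between-arm imbalance, so the set cannot be fixed in advance and intervals come out too wide; the PDA scale is also left open

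*Protocol article*

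**What the plan says.** All references are to the protocol article.

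- **Outcomes {12}** defines the primary outcome as PDA at 3 months with adjustment for baseline PDA. That covariate is unconditional.
- **Statistical methods {20a}** gives linear regression with adjusted mean differences as the default for continuous outcomes. On covariates it says: "If substantial baseline imbalances exist in characteristics that are likely to affect outcomes, these will be adjusted a priori to the outcome analyses", and then, for every model: "All models will be adjusted for baseline characteristics that differ between the arms as determined by the descriptive analysis and the baseline measures". The same section rules out P values for judging baseline differences, because these are taken to be random.
- **On scale, {20a}** adds: "Before analysis, distributions of all outcome variables will be inspected, and if necessary, transformations or other modelling options will be considered". The PDA row of Table 3 reads: "Proportion of past 14 days on which participant was abstinent; analysis based on distribution".
- **Sample size {14}** is built on a difference in means, "55% in the EUC arm vs 68% in the CHANGE arm", with PDA "distributed with a standard deviation of 37% in both arms".
- **Safeguards:** the statistical analysis plan is to be approved before unmasking and analysis ({20a}), and the trial statistician stays masked until the primary analysis is complete ({17a}).

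**The concern.** A covariate set that depends on which characteristics turn out to differ between the arms is not a priori, although {20a} uses that term. It needs a baseline table by arm, at least with coded arms. An analysis plan approved before any such comparison can repeat the rule but cannot name the covariates. With P values rightly excluded and no threshold or list given, the choice is a judgement about differences that the protocol itself regards as chance.

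The statistical cost is as follows. When a prognostic covariate is left out because it happened to be balanced, the model's standard error still counts that covariate's variance as if it could have been imbalanced. The reported interval is then wider than the real uncertainty, and precision available from baselines already collected goes unused.

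The second matter is the scale. The trial is sized on a difference in mean PDA in percentage points. If PDA is transformed, or modelled on another scale without returning to that difference, the primary result answers a different question from the one the trial was powered for.

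**Working it through.** **Inputs from the protocol ({14}).** Means 55% and 68% (difference 13 points), SD 37, alpha 0.05 (taken as two-sided), 250 per arm, 20% loss, so 250 × 0.8 = 200 per arm analysed.

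**Reproducing the plan's own figure.**
- n per arm = 2 × (1.960 + 1.282)² × 37² / 13² = 170.2, so 171. Divided by 0.8 this is 214 per arm, 428 in total.
- At 200 per arm the unadjusted SE is 37 × √(2/200) = 3.70, and 13/3.70 = 3.51 gives 94.0% power.
- The stated 90% is therefore on the cautious side. This is a separate matter and does not affect the point here.

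**Assumptions (not in the protocol).** Correlation 0.5 between baseline and 3-month PDA; five further independent covariates, each explaining 4% of variance (20% jointly); a further covariate enters if its standardised difference exceeds 0.1; baseline PDA always in the model.

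**Closed-form check.**
- Baseline PDA only: 37 × √(1 − 0.25) × √(2/200) = 3.20.
- Baseline PDA plus all five: 37 × √(1 − 0.25 − 0.20) × √(2/200) = 2.74.
- Imbalance rule: a standardised difference has standard error √(2/200) = 0.1, so P(|difference| > 0.1) = P(|Z| > 1) = 0.317. On average 5 × 0.317 = 1.59 covariates enter. The reported SE is then about 37 × √(0.75 − 0.04 × 1.59) × √(2/200) = 3.07.

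**Simulation under the null (6,000 trials).**

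| Model | Mean reported SE | Actual SE of estimate | Rejects at 5% |
|---|---|---|---|
| Baseline PDA only | 3.21 | 3.17 | 5.0% |
| Baseline PDA + imbalance-selected | 3.08 | 2.81 | 3.3% |
| Baseline PDA + all five, prespecified | 2.76 | 2.70 | 4.5% |

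The simulation error on a 5% rejection rate is √(0.05 × 0.95/6000) = 0.28 percentage points, so 4.5% is compatible with 5% and 3.3% is not. With a true difference of 13 the mean estimate is 13.0 under all three models.

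- Reported over actual SE for the imbalance rule: 3.08/2.81 = 1.10, about 10% too wide.
- Reported SE against prespecification: 3.08/2.76 = 1.12, about 12% wider.
- Actual SE against prespecification: 2.81/2.70 = 1.04, about 4% larger. Most of the cost therefore lies in the interval that is reported.

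**Scale.** Take PDA as a count of 14 days with a beta-binomial shape (an assumption) and the protocol's means and SD. The share of men at exactly 0% or 100% is then 12.7% + 19.9% = 32.6% in EUC and 9.6% + 39.5% = 49.1% in CHANGE. The same 13-point mean difference becomes:
- odds ratio (0.68/0.32)/(0.55/0.45) = 1.74;
- ratio of means 0.68/0.55 = 1.24;
- back-transformed arcsine means of 57% and 76%, about 18 points apart;
- medians of 8/14 = 57% and 12/14 = 86%, about 29 points apart.

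None of these is the 13-point contrast. An untransformed Welch comparison on similarly shaped 14-day data kept type I error at 4.3% and power at 94% in 4,000 simulated trials.

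**The case against.** The other side has several good points.

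- **Baseline PDA is already fixed**, and {20a}'s sentence ends by mentioning the baseline measures, most naturally each outcome's own baseline value. A reader might infer that all the primary model's covariates are picked by imbalance. The text does not support that; the rule governs only the further ones.
- **One of the two sentences is limited** to substantial imbalance in characteristics likely to affect outcomes, so prognosis is not ignored. This stands, but the second sentence drops both qualifiers and applies to all models, and neither sentence names a characteristic or a cut-off.
- **The rule does not lose precision against the fixed core model.** Its reported SE of 3.08 is below the 3.21 for baseline PDA alone. It trails only a prespecified set, whose strength is assumed.
- **Poor calibration might suggest false positives or bias.** The check shows neither: a mechanical rule is conservative and unbiased. Discretionary selection was not simulated.
- **The scale could still be settled in the analysis plan**, under masking, and linear regression is already the default. This is why the scale is the secondary part. A reader might also infer that a transformation is bound to follow, because PDA is likely to pile up at 0% and 100%. The protocol transforms only if necessary, and visible non-normality does not make it necessary when the untransformed comparison performs well.

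The covariate rule itself is not answered. It is a stated instruction, and no plan approved before a by-arm comparison can turn it into a named list.

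**Conclusion.** The point holds in a limited form and is worth correcting. Section {20a} makes the choice of covariates beyond baseline PDA depend on observed imbalance, without list or threshold, and calls this a priori. Under the stated assumptions, reported standard errors are about 10% larger than the actual ones and about 12% larger than prespecification would give (3.08 against 2.76). The null rejection rate is about 3.3% instead of close to 5%. The effect is modest: simulated power for 13 points stays above 94% and the estimate is unbiased. Covariates weaker than assumed would shrink the cost and stronger ones would raise it; the protocol gives no figures to settle which.

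On scale, the open wording permits a primary estimate other than the 13-point mean difference, but does not commit the trial to one.

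**What to change.** 1. Name a short list of prognostic baseline covariates for the primary model, included whatever the imbalance: baseline PDA plus others the sponsor chooses from those collected, for example AUDIT and K10. Because AUDIT is restricted to 8–19 by eligibility, its prognostic value should be weighed before it is chosen. For each secondary outcome, state explicitly that its own baseline value is included where measured.
2. Remove the imbalance-triggered rule from the main models and keep it, if wanted, as a sensitivity analysis. Drop the a priori wording attached to it.
3. Fix the difference in mean PDA, in percentage points, as the primary estimate: linear regression on untransformed PDA with heteroscedasticity-robust standard errors, or marginal standardisation back to that difference if another model is used. Replace the distribution-dependent entry for PDA in Table 3, and keep transformed models as sensitivity analyses.

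The cost is wording in the protocol and the analysis plan. The example covariates are already collected, and recruitment is expected to finish in 2026, so the change can be made before unmasking.

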### Interim analyses {21b}

No interim analysis of outcomes is planned.

### Methods for additional analyses {20b}

An economic evaluation will be carried out and will be reported following the Consolidated Health Economic Evaluation Reporting Standards [40]. A cost-effectiveness analysis will be conducted in which an estimation will be made for each participant regarding the intervention costs, disability adjusted life years (DALY) averted and quality adjusted life years (QALY) gained. We will estimate the incremental cost-effectiveness ratios, and a cost-effectiveness plan and acceptability curve will be produced to represent uncertainty. A deterministic sensitivity analysis will be carried out on assumptions made with regards to duration of effect and discount rates. The cost-effectiveness evaluation will be done against a pre-determined threshold and will be compared to other available programs that similarly aim to address alcohol misuse and mental health in Ukraine.

Furthermore, the qualitative data will be transcribed and analysed in the language of the interview (i.e. Ukrainian or Russian spoken in Ukraine). A thematic analysis will be done. The analysis will be done in NVivo © QSR International.

### Methods in analysis to handle protocol non-adherence and any statistical methods to handle missing data {20c}

Data related to outcomes and covariates will be examined for any missing entries, and if the proportion of missing data exceeds 10%, multiple imputation methods may be employed. The results will be presented following the CONSORT guidelines [39], and intention to treat principles will guide the primary analysis of the findings.

### Plans to give access to the full protocol, participant level-data and statistical code {31c}

The participant-level dataset will not be shared due to concerns raised during the feasibility trial, including fears of conscription and access to the data by Russian intelligence. Consequently, consent forms for the full trial were updated to state that data would not be made available to third parties.

## Oversight and monitoring

### Composition of the coordinating centre and trial steering committee {5d}

The trial will be supported by the same Trial Steering Committee (TSC) and Trial Management Committee (TMC) as for the comparison Uganda trial [23]. The TSC will meet every 6 months and will be responsible for the overall governance and oversight of the trial ensuring the conduct is aligned with the protocol and relevant regulations. The TSC is composed of experts on alcohol misuse, mental health and psychosocial support, providing mental healthcare in humanitarian settings and epidemiologists with relevant experience in conducting trials in war-affected settings. On the other hand, the TMC will meet bimonthly and is responsible for providing country-specific advice. It is composed of the PI (DF), and the site PI (SB), who will report to the DSMB and funder regarding the progress of the trial. Furthermore, the field coordinator and work package leads will join the TMC meetings to provide updates on progress.

### Composition of the data monitoring committee, its role and reporting structure {21a}

The CHANGE project is regulated by a DSMB who will meet twice a year to discuss this trial and the trial in Uganda [23]. The members of the DSMB are independent from the TMC and TSC, and are responsible for monitoring the progress of the RCT. The DSMB is composed of the Chair who is a clinical subject matter expert, an independent trialist and statistician, and a second independent clinical subject matter expert. They are the only committee that has access to the unmasked data during the ongoing trial. During the DSMB meetings, the committee will be responsible for deciding whether there are any safety issues within the CHANGE project, report to the TSC and recommend on the continuation of the trial, and consider any requests for the release of the trial data. A DSMB charter is available upon request to the authors.

### Adverse event reporting and harms {22}

The possibility of adverse events which are related to the CHANGE intervention is considered low, and protocols have been developed to identify and address different types of adverse events. From previous experience during the COVID-19 pandemic, during which the service delivery transitioned to a remote format, services to war-affected populations were provided remotely [41]. During that time, adverse events were documented, recognizing the heightened distress associated with war experiences. Remote referral pathways were established, including a comprehensive database of remote service providers, with a preference for in-person referrals where feasible, to connect individuals with additional services, notably psychiatric evaluations and prescriptions. In the current trial, these standard operating procedures will be maintained, namely all members of the clinical team have undergone training in safety protocols for remote service delivery, ensuring adherence to best practices. For high-risk cases, regular check-ins will be conducted to monitor and address evolving situations. The responsible for carrying out these check-ins will depend on the nature of the case (e.g. a psychiatrist or a psychologist). In the past, a limitation of remote service delivery was encountered when clients with potential risks declined to provide detailed contact information, which could impede timely engagement with additional services, such as emergency medical assistance. For the current trial, if a client is considered to be at risk of an AE or SAE, we will request consent for having the contact number of a family member or someone from the clients’ personal sphere to mitigate this risk.

A critical incident register will be maintained during the study to record specific SAEs and AEs. An overview of the types of SAEs and AES can be found in Table 5. SAEs and AEs that are detected during any of the outcome assessments or intervention sessions will be disclosed immediately to the local research director and site PI who will become unmasked. For each individual event, a report will be written. Based on the type of event, the participant will be asked to give consent for further evaluation, assessment, and/or follow-up by a designated health professional (see Table 6). If the participant experiencing an AE or SAE was in the intervention arm of the trial, and once they are referred to further care their data will be excluded from the analysis. Nonetheless, if they are able to, they can receive further CHANGE sessions. The exception to this is referrals for intimate partner violence, whereby participants will be encouraged to access protection services, but will not be excluded from the analysis.

**Table 5 Tab5:** Expected and unexpected SAE and AEs (adapted from Van Der Boor et al., 2024 [23])

	Expected	Unexpected
SAE	Victimization (violence against the trial participant or nuclear family)	Death of the trial participant due to suicide
	IPV (violence against family members by participant, or violence against participant by family member)	Death of the trial participant due to other causes
	Suicide attempt	Hospital admission of trial participant due to a psychiatric problem
	Homicidal ideation	Planning and/or going through with the homicidal ideation
	Stigmatisation	Hospital admission of trial participant due to other causes (i.e. serious medical emergency)
	Serious lack of food / Critically unsatisfied basic needs	
AE	Clinical deterioration of the participant	
	Emotional distress caused by a trial procedure (either by the outcome assessment or the intervention delivery)

**Table 6 Tab6:** SAE referral according to intervention arm

SAE	Reported at outcome evaluation in both arms, referral to:	Reported by facilitator in the intervention arm only, referral to:
Hospital admission of participant due to serious medical emergency^a^	General physician (GP), family doctor	GP, family doctor
Hospital admission of participant due to a psychiatric problem	Independent psychiatrist, Psychiatrist in the hospital	Independent psychiatrist, Psychiatrist in the hospital
Victimisation (violence against the participant)	Independent psychologist, social worker, humanitarian agency representative	Intervention supervisor
Severe IPV perpetrated by participant (violence against family members by participant) that includes a risk of severe injury and/or death	Independent psychologist, social worker, humanitarian agency representative	Intervention supervisor
Suicide attempt	Independent psychiatrist, Psychiatrist in the hospital	Independent psychiatrist, Psychiatrist in the hospital
Homicidal ideation	Independent psychiatrist, Psychiatrist in the hospital	Independent psychiatrist, Psychiatrist in the hospital
Stigmatization^a^	Intervention supervisor	Intervention supervisor
Death of the trial participant	N/A	N/A
Any violence toward others	Independent psychiatrist, social worker, humanitarian agency representative	Independent psychiatrist,
Serious lack of food/ Critically unsatisfied basic needs	GP, primary health care worker (nurse/ midwife)	GP
**AE**		
Clinical deterioration of trial participant, including a high risk of a suicide attempt	Independent psychiatrist, Psychiatrist in the hospital	Independent psychiatrist, Psychiatrist in the hospital
Emotional distress caused by a trial procedure (either by the outcome assessments or the intervention delivery)	Independent psychologist, Psychiatrist in the hospital	Independent psychologist, Psychiatrist in the hospital

^a^Prior to referral to the nominated healthcare professional, these SAEs will have an independent clinician review the SAE narrative to determine if this is indeed a SAE

During the 3-month follow-up assessment, all participants will be asked to respond to the safety questions (related to suicide and homicidal ideation) again. In the case of an SAE detection, an independent psychiatrist will assess the participant, and the SAE report will be completed. Participants with safety issues identified during the follow-up will not be excluded from the trial. These questions aim to identify any problems and provide timely referral pathways.

When an SAE is related to stigma, a report will be written as described above, and an evaluation will be conducted by an independent healthcare provider to ensure quality and correct identification of these types of SAEs. Irrelevant of the cause, for events determined by the independent clinician to be SAEs, the person who became aware of the event (outcome assessor or facilitator) will then forward the SAE for further referral to the appropriate professional. The time from initial detection of a potential SAE by the research team (e.g. outcome assessors and facilitators), to the responsible team member (outcome assessor or facilitator) sending the SAE/AE report to the nominated health professional is two working days. Following these 2 days, if it classifies as an SAE, the responsible team member will inform the research director, who will prepare and submit the report to the site PI, who will send it to overall PI, DSMB and respective ethics committees within 5 working days of detection. All SAEs and AEs will be followed up until they have abated, or until a stable situation has been reached. AEs will not be reported to the DSMB but will be included in the annual ethics report.

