**Methods:**

This study is a parallel-arm, single-blind, individually randomised controlled trial across Ukraine government-controlled territories. Following informed consent, we will recruit 500 adult war-affected men, randomised 1:1 to EUC and CHANGE, or EUC alone. Inclusion criteria include elevated levels of alcohol use (between 8 and 19, inclusive, on the Alcohol Use Disorder Identification Test); psychological distress (≥ 16 on the Kessler Psychological Distress Scale) and ability to speak Ukrainian or Russian. CHANGE will be delivered over 6 weeks by 14 community-based facilitators, with outcomes assessed at 3 months post-randomisation. The primary outcome for CHANGE is the PDA from alcohol at 3 months, measured using the Timeline Follow Back. Secondary outcomes include percentage days of heavy drinking, alcohol misuse, psychological distress (depression, anxiety, and posttraumatic stress disorder), functional disability, intimate partner violence perpetration and health economics indicators at 3 months. The primary analysis will follow an intention-to-treat approach. A mixed-methods process evaluation will examine facilitator competency, recruitment, retention/completion, appropriateness, dose received, fidelity and feasibility of delivery and acceptability.

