### Intervention description {11a}

In addition to being offered EUC as described above, participants randomised to the intervention arm will be offered six sessions of the CHANGE intervention in a remote format. Based on the feasibility trial, an additional booster session may be included that focuses on reviewing the previously taught strategies (without introducing new ones) that can be provided to participants with high stress levels, providing extra time to practice and internalize them. A convenient online platform for the call will be agreed upon with the participants. These can include, but are not limited to, Zoom, Google Meets, Skype, Telegram or Viber.

The CHANGE intervention is a brief, transdiagnostic psychological intervention, informed by PM + and enhanced through strategies based on empirical evidence, which aim to address alcohol misuse [22, 23]. The initial PM + intervention uses strategies including problem solving, stress management, behavioural activation and accessing social support to address common mental health problems [18]. To develop the CHANGE intervention targeting alcohol misuse, firstly a meta-review was conducted [28] to identify evidence-based strategies for the management of AUDs. After this a systematic intervention adaptation process followed to incorporate strategies into PM + that address alcohol misuse including enhancing motivation to change drinking behaviours. CHANGE is composed of three phases each which include individual weekly sessions of approximately 90 min each with the facilitators (Table 1).

**Table 1 Tab1:** Outline of the three phases and psychological strategies included in each phase of CHANGE

Phase I	Phase II	Phase III
• Engaging the client • Assessments • Review from the assessments • Information about the CHANGE intervention • Understanding adversity • Understanding alcohol use • Goal setting for drinking • Specifying a change plan	• Changing drinking behaviours • Managing stress • Managing emotions • Managing problems • Behaviour activation • Strengthening social support	• Relapse prevention • Ending the intervention • Optional booster session
Basic helping and motivational skills		

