### Criteria for discontinuing or modifying allocated interventions {11b}

If clinical deterioration, an adverse event (AE) or a serious adverse event (SAE) is detected throughout the course of the trial by an outcome assessor or facilitator, it will be promptly reported to the research team, trial sponsor, ethics committees and Data Safety and Management Board (DSMB), see Sect. 22 for further details. Where an AE or SAE occurs, participants will be referred to specialist support if deemed necessary by the research director and research team using previously developed remote referral pathways. Clinical deterioration includes instances where a participant is intoxicated during multiple sessions, reports suicidal ideation, or homicidal ideation. Participants who report suicidal ideation will only be referred to specialist services or withdrawn from the trial if they are at imminent risk of suicide, which involves having a plan in place. Participants referred to specialist support during baseline outcome assessment or the CHANGE intervention sessions will be withdrawn from the trial but may continue to receive the remaining CHANGE sessions. If participants are referred to specialist support at the 3-month outcome assessment, they will not be withdrawn from the trial. All facilitators and outcome assessors have received training in safety protocols for remote service delivery and to ensure adherence to best practice.

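### Safety events have an extra detection route in the CHANGE arm only, so crude event counts by arm are not comparable and probably lean against CHANGE

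*Protocol article*

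**What the plan says.** Section {22} of the protocol article sets up a critical incident register and passes on "SAEs and AEs that are detected during any of the outcome assessments or intervention sessions". Table 6 gives facilitator reports a column of their own, headed "Reported by facilitator in the intervention arm only, referral to". Section {11b} names the same two detectors: an event counts when it "is detected throughout the course of the trial by an outcome assessor or facilitator". The EUC specialist is not named.

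The contact schedule differs by arm. Under section {11a}, CHANGE participants "will be offered six sessions of the CHANGE intervention in a remote format", weekly and about 90 minutes each, and "an additional booster session may be included". EUC is one consultation, offered to both arms (sections {6b} and {11a}). Outcome assessments take place at baseline and at 3 months only (section {12}).

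Section {11b} also states: "Clinical deterioration includes instances where a participant is intoxicated during multiple sessions". Table 5 lists clinical deterioration as an AE.

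Under section {21a}, when the DSMB meets, "the committee will be responsible for deciding whether there are any safety issues within the CHANGE project". It also recommends on continuation and is the only committee with unmasked data during the trial. On what reaches it, the article disagrees with itself. Section {11b} has clinical deterioration, AEs and SAEs promptly reported to the DSMB among others. Section {22} says that AEs go into the annual ethics report and not to the DSMB.

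**The concern.** A comparison of harms between arms is interpretable only if an event has a similar chance of being recorded in each arm. Here a disclosure of victimisation, stigma, unmet basic needs or suicidal thoughts in week 3 can be recorded through a facilitator in CHANGE. In EUC it waits for the 3-month assessment and depends on whether it is asked about and recalled there. One named component of an AE category has no counterpart in EUC at all.

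If crude counts are tabulated by arm, an excess in CHANGE has two possible explanations, harm or contact time. Believing the excess could lead to a wrong safety conclusion. Dismissing it as a detection effect could hide a real harm. If the source of each event is not recorded when it is found, later analysis cannot separate the two.

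**Working it through.** The article gives no event rate and no planned harms test, so there is no figure of its own to reproduce. The check counts detection occasions and then shows what they could do under stated assumptions.

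**Inputs from the article.** 250 per arm (section {14}); six weekly sessions plus an optional booster ({11a}); "CHANGE will be delivered over 6 weeks by 14 community-based facilitators" (abstract, Methods); one assessment after randomisation, at 3 months ({12}); safety questions on suicide and homicidal ideation put to everyone again at 3 months ({22}), with a last-month look-back in the screening wording ({10}). Three months is taken as 13 weeks.

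**Assumptions, not in the article.** Equal true 3-month risk p in both arms, 5% to 20%; probability c that the 3-month assessment recovers an event, 33% to 100%; probability s that any one session detects it, 0 to 30%.

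**Step 1: occasions after randomisation.** EUC: 1. CHANGE: 1 + 6 = 7, or 8 with the booster.

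**Step 2: calendar coverage of the suicide and harm questions only.** If the last-month wording is kept, the 3-month assessment covers 13/3 = 4.33 weeks.
- EUC: 4.33/13 = 33%.
- CHANGE, six sessions: (6 + 4.33)/13 = 79%; ratio 10.33/4.33 = 2.4.
- CHANGE, seven sessions: (7 + 4.33)/13 = 87%; ratio 11.33/4.33 = 2.6.
- If six sessions pick up only a fraction f of events in their own weeks, the ratio is (4.33 + 6f)/4.33, which is 1.42, 1.69 and 2.11 for f = 0.3, 0.5 and 0.8.

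This step does not carry over to other event types. Perpetration of intimate partner violence is asked about in both arms over the last 3 months (Table 3), and no look-back is given for the rest.

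**Step 3: general model.** Detection in EUC is c. Detection in CHANGE is d = 1 − (1 − c)(1 − s)^6. The ratio of expected counts is d/c, whatever the value of p. Example: c = 0.33 and s = 0.10 give d = 1 − 0.67 × 0.531 = 0.644, and 0.644/0.33 = 1.95.

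| c | s = 0.05 | s = 0.10 | s = 0.30 |
|---|---|---|---|
| 0.33 | 1.54 | 1.95 | 2.79 |
| 0.50 | 1.26 | 1.47 | 1.88 |
| 0.80 | 1.07 | 1.12 | 1.22 |
| 1.00 | 1.00 | 1.00 | 1.00 |

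At p = 10%, the cell with c = 0.33 and s = 0.10 means about 16.1 detected events in CHANGE against 8.2 in EUC. The model lets a session detect any event in the 3 months, including one that happens after the last session, so the top corner is generous.

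**Step 4: what a naive test would show.** With 250 per arm, 2,000 simulated trials per scenario, Fisher's exact test at 0.05 and s = 0.10, a nominally significant CHANGE excess without any true difference occurs as follows for p from 5% to 20%:
- c = 0.33: 14% to 59% of trials
- c = 0.50: 7% to 30%
- c = 0.80: 3% to 6%
- c = 1.00: about 2%

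**Step 5: equal ascertainment.** With s = 0, or counting only events found the same way in both arms, the ratio is 1.00 and a significant CHANGE excess occurs in about 1% to 2% of trials.

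**The case against.** The strongest reply is that the article plans no comparison of event counts by arm. Its statistical sections contain no harms analysis, the register is described as serving individual reports and referral, and tabulation may be settled in an analysis plan or DSMB charter that is not shown. Extra contact is also inherent in testing a psychological intervention against a single consultation. This stands as far as it goes: a missing harms table is not the point here. The point is that the article itself fixes a detection rule that differs by arm and an AE definition with a component only one arm can meet. Any later table inherits both.

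Several further objections are sound and limit the claim:
- Events are detected in sessions; the article describes no structured enquiry for them there. The structured safety questions described after randomisation are the same in both arms.
- Intimate partner violence perpetration has a 3-month recall instrument in both arms. Deaths and admissions are likely to become known or be recalled, so the bias there should be small. Suicidal and homicidal ideation, the other named components of clinical deterioration, can be met in either arm.
- Section {22} provides check-ins for high-risk cases without limiting them to one arm.
- Section {22} excludes CHANGE participants' data from the analysis after referral, except for intimate partner violence. If that reached the safety tables, it would push the other way.

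A reader might infer that the counts will make CHANGE look harmful when it is not. The documents support neither half: the excess may be nil if the 3-month assessment recovers everything, and the absence of true harm is unknown. A reader might also infer that the session-only criterion will mislead the DSMB. Under section {22} AEs never reach it; under section {11b} they do. Only the SAE route to the DSMB is undisputed.

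**Conclusion.** The point holds as one about comparability. After randomisation CHANGE has seven or eight scheduled detection occasions against one in EUC, and part of one AE definition cannot be met in EUC. Crude AE and SAE counts by arm are not comparable, and the probable direction is against CHANGE. The size depends mainly on how completely the 3-month assessment recovers earlier events: a ratio from 1.0 to about 2.8 with equal true risk. That range rests on assumed recall, session detection and event rates, none of them in the article, and it should not be read as a forecast. Separately, sections {11b} and {22} contradict each other on whether AEs are reported to the DSMB.

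**What to change.** 1. Add a field to the incident register for the source of every event: 3-month assessment, facilitator session, or other.
2. Base the between-arm harms comparison on events ascertained the same way in both arms: those elicited at the 3-month assessment, plus deaths and any others ascertained independently of sessions. Limiting it to the 3-month assessment alone would lose deaths.
3. Keep referred or withdrawn CHANGE participants in that comparison. State that the withdrawal rule in {11b} and the exclusion in {22} do not remove them from it; otherwise it tilts towards CHANGE looking safe.
4. List session-detected events separately for CHANGE, without an EUC comparator, so that they stay visible to the DSMB and in publication.
5. Report intoxication at sessions as a session observation, outside the compared AE category.
6. Reconcile {11b} and {22} on whether AEs go to the DSMB.

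The cost is one register field, a table rule and a clarification of the text. The compared counts will be smaller, will rest partly on recall at 3 months, and will miss non-fatal events in men lost to follow-up, for whom the sample size allows 20%. Point 3 also needs 3-month safety data from withdrawn men who agree to give them. Reporting and care of individual events do not change.
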